### Sample size estimation

2.11

The sample size has been calculated using the GRANMO program, accepting an alpha risk of 0.05 and a beta risk of 0.2. It requires 24 subjects for each group, totaling 72 patients, to detect a difference equal to or greater than 5 degrees of improvement in R1 and R3 of MTS. It is assumed that the common standard deviation is 16.44, with a correlation coefficient between the initial and final measurement of 0.91. These data have been extracted from a study on the treatment of spasticity using shockwave therapy in patients with CP (21). A follow-up loss rate of 10% will be estimated.

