**Methods:**

Following a power calculation using the minimal clinical important difference of our primary outcome (R2 of Modified Tardieu Scale), 72 patients will be included in the study. Enrolment is based upon inclusion/exclusion criteria outlined in the Methods section. Participants will be randomized in 3 groups. Each patient will receive 2000 impulses in the Triceps Sural muscle (distributed by all the plantar flexor muscles: soleus and gastrocnemius), at a 2.2 Bars pressure and a frequency of 8 Hz. The Control Group will receive 3 rESWT sessions with a time interval of 1 week between each session. The Experimental Group A will receive 3 rESTW sessions with a time interval of 2 weeks between each session and the Experimental Group B will receive 3 rESTW sessions with a time interval of 4 weeks between each session.

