### Statistical analyses

2.12

Statistical analysis of the data will be conducted using SPSS software version 23 and R-software (MLMM package). An intention-to-treat analysis will be performed. Significance level 5% (*p*-value <0.05). For the descriptive analysis, a normality check will be conducted using Shapiro–Wilk / Kolmogorov–Smirnov tests. For quantitative variables, the mean and standard deviation will be reported (in case of non-parametric data, the median and interquartile range). For qualitative variables, frequency and percentages will be reported. For inferential statistics, a mixed linear model for repeated measures will be used and adjusted as necessary for covariates such as age, sex, GMFCS, and other comorbidities that may be observed. For the qualitative analysis, semi-structured interviews will be conducted, and the following categories will be established: Physical efficacy, bodily function (subcategories: increased relaxation, mobility, balance, etc.). Autonomy, daily life activities, and functionality (frequency, intensity, location). Pain conditions (intensity, location). Rating of satisfaction with shockwave therapy. Subjective, emotional, and related aspects.

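### The inputs in section 2.11 do not give 24 per group: a two-sided 5% comparison of two groups needs about 31 evaluable, and after 10% loss the power for 5 degrees is about 63–65%, not 80%

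*Protocol article*

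**What the plan says.** Section 2.11 (Sample size estimation) of the protocol article gives the error rates as "accepting an alpha risk of 0.05 and a beta risk of 0.2" and the target as "to detect a difference equal to or greater than 5 degrees of improvement in R1 and R3 of MTS". The variability inputs are "It is assumed that the common standard deviation is 16.44, with a correlation coefficient between the initial and final measurement of 0.91", taken from an earlier shockwave study in cerebral palsy. The result is 24 per group, 72 in total: "It requires 24 subjects for each group, totaling 72 patients, to detect a difference equal to or greater than 5 degrees of improvement". The paragraph closes with "A follow-up loss rate of 10% will be estimated" and does not say whether the 24 already contains that allowance. The abstract repeats the total: "72 patients will be included in the study".

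Sidedness is not given. Section 2.12 (Statistical analyses) adds only a 5% significance level, with p below 0.05, and a mixed linear model for repeated measures adjusted for covariates as necessary.

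**The concern.** The section gives enough inputs to redo the calculation, and the usual reading of them does not return 24. A standard deviation with an initial–final correlation points to a comparison of change from baseline between two groups. An alpha of 0.05 with no further comment is conventionally two-sided. On that reading the trial is smaller than its own justification requires.

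All three arms receive active treatment and differ only in the interval between sessions. A non-significant result could therefore easily be taken to mean that the interval does not matter. A reader who believes the trial had 80% power for 5 degrees would give such a result more weight than it deserves.

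**Working it through.** **Inputs (section 2.11).** Standard deviation 16.44; correlation 0.91; difference 5 degrees; alpha 0.05; power 0.80; loss 10%. The article does not give sidedness, so both versions are shown.

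**Standard deviation of the analysed quantity.**
- Change score: 16.44 × √(2 × (1 − 0.91)) = 6.975.
- Baseline-adjusted final value: 16.44 × √(1 − 0.91²) = 6.816.

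**Can 24 be reproduced?** The formula is n per group = 2 × (z_alpha + z_beta)² × SD² / d², with z_beta = 0.842. Loss is allowed for by dividing by 0.9.

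| Test | Analysis | d | Evaluable n | With 10% loss |
|---|---|---|---|---|
| One-sided 5% | change | 5 | 24.06 | 26.7 |
| One-sided 5% | adjusted | 5 | 22.98 | 25.5 |
| Two-sided 5% | change | 5 | 30.55 | 33.9 |
| Two-sided 5% | adjusted | 5 | 29.17 | 32.4 |
| Two-sided 5% | change | 6 | 21.21 | 23.6 |

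For the main two-sided case: 2 × (1.960 + 0.842)² × 6.975² / 25 = 30.55, so 31. Rounding before or after the loss step gives 34–35 per group for change scores and 33–34 with baseline adjustment.

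Two rows match the stated 24. One is the one-sided change-score test with no loss allowance (24.06, strictly 25 when rounded up). The other is the two-sided test for 6 degrees with loss (23.6). The first leaves out the stated loss rate and relies on a one-sided test that is not disclosed. The second uses a difference other than the stated 5.

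Other routes do not help. A within-group paired comparison needs 15.3 two-sided (17.0 with loss) or 12.0 one-sided (13.4 with loss). Ignoring the correlation needs 170 two-sided or 134 one-sided.

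**Power with the stated 24 per group, d = 5.** These are noncentral-t values for one pair of groups. After 10% loss, 24 × 0.9 = 21.6 are evaluable.

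| Test | Analysis | 24 evaluable | 21.6 evaluable |
|---|---|---|---|
| Two-sided 5% | change | 68.1% | 63.3% |
| Two-sided 5% | adjusted | 70.1% | 65.3% |
| One-sided 5% | change | 78.9% | 74.9% |
| One-sided 5% | adjusted | 80.5% | 76.6% |

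**Difference detectable with 80% power, two-sided.** For change scores it is 5.8 degrees with 24 evaluable and 6.1 with 21.6. With baseline adjustment it is 5.6 and 6.0.

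**The case against.** **The test may have been one-sided.** The article never says two-sided, and its working hypothesis is directional: longer intervals may prolong benefit. A one-sided 5% calculation without loss gives 24.06, so the 24 is not inexplicable. This stands, and it means the two-sided shortfall cannot be asserted without stating that assumption. It does not rescue the section. The same paragraph states a 10% loss, and with it the one-sided test needs 25.5–26.7 per group and has about 75–77% power.

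**The planned analysis is not a single change-score comparison.** Section 2.12 plans a mixed model, and section 2.7 lists five post-baseline visits. Suppose the correlation is 0.91 between all visits and the group effect is averaged over the five visits with baseline adjustment (both assumptions). The standard deviation is then 16.44 × √((1 + 4 × 0.91)/5 − 0.91²) = 5.20, and two-sided power for 5 degrees is about 90% with 24 and 87% with 21.6. This also stands as a limit. A reader might infer that the trial itself misses a true 5-degree effect one time in three, and the documents do not support that. Equally, they do not name an averaged contrast. The aim is prolongation, and a contrast at a single late visit would not gain in this way.

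**Five degrees and the minimal clinically important difference.** A reader might also infer that power is low at exactly that difference. The abstract ties the calculation to that difference for R2, while section 2.11 applies 5 degrees to R1 and R3. No section says that 5 degrees is the minimal clinically important difference.

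**Multiplicity and a weaker correlation.** Adjusting for three pairwise comparisons, or assuming a correlation below 0.91 at 24 weeks, would lower power further. The article plans no such adjustment and gives no other correlation, so the point does not rest on either.

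**Conclusion.** The point holds as a fault in the stated calculation. With all the inputs of section 2.11, including the 10% loss, every version of a two-group comparison at one final time point needs more than 24 per group: 25.5–26.7 one-sided and 32.4–33.9 two-sided, before rounding up. Power for 5 degrees after loss is about 63–65% two-sided and about 75–77% one-sided, against the stated 80%.

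The size of the shortfall depends on sidedness, which the article does not state; two-sided is the conventional reading. The figures assume normal outcomes, equal groups, one pairwise comparison and the quoted standard deviation and correlation. They describe the calculation in section 2.11, not the power of the mixed model.

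**What to change.** Keep 72 patients and correct section 2.11. First establish from the original GRANMO entry, and then state:

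- whether the test was one- or two-sided;
- which comparison was powered (which groups, and change or baseline-adjusted value);
- which difference was entered;
- whether 24 is before or after the 10% loss.

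Then restate the power to match. If two-sided: 24 enrolled per group with 10% loss gives about 80% power for about 6 degrees and about 63–65% for 5 degrees, per pairwise comparison. If one-sided: about 75–77% for 5 degrees after loss, with the one-sided test declared in section 2.12 as well. If 6 degrees was the value entered, correct the 5.

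The cost is a rewritten paragraph, matching changes wherever the calculation is repeated, and a less favourable stated power. Recruitment does not change.

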### Statistical analyses

2.12

Statistical analysis of the data will be conducted using SPSS software version 23 and R-software (MLMM package). An intention-to-treat analysis will be performed. Significance level 5% (*p*-value <0.05). For the descriptive analysis, a normality check will be conducted using Shapiro–Wilk / Kolmogorov–Smirnov tests. For quantitative variables, the mean and standard deviation will be reported (in case of non-parametric data, the median and interquartile range). For qualitative variables, frequency and percentages will be reported. For inferential statistics, a mixed linear model for repeated measures will be used and adjusted as necessary for covariates such as age, sex, GMFCS, and other comorbidities that may be observed. For the qualitative analysis, semi-structured interviews will be conducted, and the following categories will be established: Physical efficacy, bodily function (subcategories: increased relaxation, mobility, balance, etc.). Autonomy, daily life activities, and functionality (frequency, intensity, location). Pain conditions (intensity, location). Rating of satisfaction with shockwave therapy. Subjective, emotional, and related aspects.

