### Study design

2.1

This clinical trial is designed as a single-center randomized clinical trial with three parallel groups. This protocol follows the Consolidated Standards of Reporting Trials (CONSORT) Statement on randomized trials and it will be conducted according to the Recommendations for Interventional Trials (SPIRIT). A flowchart overview of the study is presented in Figure 1. The Standard Protocol Items: SPIRIT table for enrolment, interventions, and assessments is presented in Table 1.

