### Outcome measures

2.7

Primary outcome measures: Spasticity of the treated muscles assessed with the Modified Tardieu Scale (MTS). Secondary outcome measures: Goal Attainment Scale (GAS), Timed Up and Go Test (TUG), 10 Meter Walk Test (10-MWT), Point shear wave elastography (pSWE), satisfaction with the therapy, and adverse effects. Prior to the first rESWT session, the blinded evaluating physiotherapist and his assistant will conduct a baseline assessment (t0) of all outcome variables and other aspects deemed appropriate as reference for assessing goal achievement. These assessments will be repeated across all intervention groups at 3 weeks from the start of treatment (t1), 5 weeks from the start of treatment (t2), 9 weeks from the start of treatment (t3), 12 weeks from the start of treatment (t4), and 24 weeks from the start of treatment (t5).

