#### Modified Tardieu Scale

2.8.1

The main variable of the study will be the physiological response of spasticity in the treated muscle, assessed using the Modified Tardieu Scale (MTS). This test is based on the evaluation of muscular resistance to passive stretching at two different speeds: slow speed (V1) and fast speed (V3), to quantify the joint angles at which such resistance appears. The V1 stretch is used to determine the angle of muscle resistance at low speed (R2), equivalent to the passive range of motion (pROM) and the V3 stretch is used to determine muscle resistance at high speed (R1) or catch reflex. The MTS it could be more sensitive than other measures in assessing spasticity. Its inter- and intra-rater reproducibility is acceptable (25). All measurements were conducted using a inclinometer to determine the angular value of the two segments. For the measurement of calf muscles, separate stretches were applied to the gastrocnemius muscle (measured with the knee extended) and the soleus muscle (measured with the knee flexed at 90°).

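### The single 5% level and the unsplit alpha of 0.05 belong to no defined primary test: three arms, inconsistently named primary angles, two muscles and five post-baseline visits are left open

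*Protocol article*

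**What the plan says.** - **Threshold (2.12).** One level is given, "Significance level 5"%, with p below 0.05 as the criterion. The inferential method is a linear mixed model for repeated measures with covariates as needed. No model term, arm contrast or visit is named as deciding.
- **Sample size (2.11).** The calculation is made "accepting an alpha risk of 0.05 and a beta risk of 0.2". The stated requirement is 24 per arm, or 72 in all. The target effect is given as "a difference equal to or greater than 5 degrees of improvement in R1 and R3 of MTS". The SD input is 16.44, the first and last measurements are taken to correlate 0.91, and 10% loss is expected. Sidedness and the arm contrast are not stated.
- **Arms (2.1).** The trial is a "single-center randomized clinical trial with three parallel groups": control (CG) and experimental groups A (EGA) and B (EGB).
- **Primary outcome.** The abstract's Methods paragraph gives R2 alone. Section 2.7 reads "Primary outcome measures: Spasticity of the treated muscles assessed with the Modified Tardieu Scale (MTS"), with no angle, muscle or visit. Section 2.8.1 defines R1 (fast stretch) and R2 (slow stretch), and says "separate stretches were applied to the gastrocnemius muscle (measured with the knee extended) and the soleus muscle". It defines no R3.
- **Visits (2.7).** Weeks 3, 5, 9, 12 and 24 after the start of treatment, all with equal standing.

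**The concern.** A significance level controls error only for a stated test. Here the reader cannot tell which result would confirm that a longer interval prolongs benefit: which of the three arm contrasts, which angle, which muscle position, which week. The article's statements about the angle also disagree with each other. If several results could each count as success at 0.05, the trial's chance of a false claim exceeds the 5% on which it was sized, and the choice of the result to stress could be made after the data are seen. The sample size contains no allowance for this, so a later split of alpha would have to be paid for in power.

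**Working it through.** **1. Reproduce the planned 24 per group.**
SD of change = 16.44 × √(2 × (1 − 0.91)) = 6.97.
n per group = 2 × SD² × (z_α + z_β)² / 5².
- One-sided 0.05, 80% power: 2 × 48.65 × (1.645 + 0.842)² / 25 = 24.06, in effect the stated 24, before any loss.
- Two-sided 0.05: 2 × 48.65 × (1.960 + 0.842)² / 25 = 30.5, so 31, or 31/0.9 → 35 with 10% loss.
- Baseline-adjusted, SD = 16.44 × √(1 − 0.91²) = 6.82: 23 one-sided (26 with loss), 30 two-sided (34 with loss).

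The stated figure therefore fits one two-group comparison at an unsplit, one-sided 0.05. No two-sided or three-group variant that was tried returns 24.

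**2. Power at 24 per arm, two-sided 0.05, one contrast.**
Standard error = 6.97 × √(2/24) = 2.01, and 5/2.01 = 2.48. The t-based power is 68% (normal approximation 70%). With 10% loss (21.6 per arm) it is 63% (normal approximation 65%). Baseline adjustment changes this little: 72% and 67% by the normal approximation.

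**3. False-positive risk from the arms alone** (one angle, one muscle, one visit, no true difference, each contrast at two-sided 0.05).
- Independent tests would give 1 − 0.95² = 9.8% for two and 1 − 0.95³ = 14.3% for three.
- The contrasts share arms, so the true values are lower. Simulation gives 9.0% for EGA and EGB each against CG, and 12.1% for all three pairs.

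These two figures need no assumed correlation between outcomes. They follow from equal arms.

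**4. Wider families.** The article gives no correlation between visits, angles or muscles, so values of 0.5 to 0.9 are assumed and the range is shown. A correlation of 0.5 between changes at two visits would follow if every pair of visits correlated 0.91, but 2.11 states 0.91 for the first and last measurement only.

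| Tested separately at 0.05 | Two contrasts with CG | Three pairs |
|---|---|---|
| One angle, one muscle, one visit | 9% | 12% |
| Two angles, one muscle, one visit | 13–16% | 17–21% |
| Two angles, two muscles, one visit | 17–28% | 23–36% |
| One angle, one muscle, five visits | 18–31% | 23–39% |
| One angle, two muscles, five visits | 24–50% | 30–60% |
| All: 2 × 2 × 5 = 20 measures (40 or 60 tests) | 31–72% | 39–82% |

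**5. A joint test instead.** One three-group test on one named measure has a 5% error. It keeps that only if the measure is fixed. One joint group test per measure, averaged over the five visits, gives 8–9% over R1 and R2 and 12–16% over the four angle-by-muscle measures (assumed correlation 0.5 between visits and 0.5–0.8 between measures).

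**The case against.** The strongest reply has three parts.

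*The article does not describe dozens of separate tests.* This stands. A reader might infer that 60 primary tests are planned, that the 5% level is therefore certainly lost, and that a chance finding is likely. The documents do not support that. Section 2.12 gives a significance level, not a rule that any one positive result proves the hypothesis. It names a repeated-measures mixed model, which can test groups over all visits in one term. The abstract confines the primary outcome to R2. The last row of the table is an outer case that also rests on assumed correlations.

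*Test hierarchies are commonly left to the analysis plan, which is not shown.* This stands as far as the mere absence of a multiplicity procedure goes. It does not cover what the article itself states: three incompatible accounts of the primary angle, one of them using a label that 2.8.1 never defines, and a sample size that spends all of its alpha on one unnamed contrast.

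*Putting EGB first is a preference.* This stands too. The hypothesis in section 3 concerns any interval beyond one week, and so covers EGA and EGB alike. The order is for the sponsor to choose, provided it is fixed beforehand.

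**Conclusion.** The concern holds in a limited form: the 5% level in 2.12 and the alpha in 2.11 are attached to no defined primary test. The firm part of the size is 9% to 12%, on the condition that either or any arm contrast may count as success on a single measure at a single visit. With R2 in one muscle tested at each of five visits it would be roughly 18% to 40%, and with every combination tested up to about 80%. Both depend on correlations that the article does not give. A single joint test on one named measure would keep 5%, so inflation is a risk that the text leaves open and not an established property of the analysis. Separately, the power of 80% is reached only for one one-sided comparison without loss. The two-sided figures of 68% and 63% rest on the plan's SD and correlation, and on their applying to whichever measure is chosen.

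**What to change.** **In 2.12**, within the planned mixed model:
- Name one primary measure. R2 agrees with the abstract. State whether the gastrocnemius and soleus positions are averaged or which one is used.
- Name one primary visit. Week 24 is the one that section 3 uses to justify the longer follow-up.
- Protect the arm contrasts at an overall two-sided 5% by a pre-stated rule. One option is a fixed sequence, for example EGB vs CG, then EGA vs CG, then EGB vs EGA, stopping at the first p of 0.05 or more. Another is a joint three-group test that must be significant before the pairwise tests are read.
- Report other angles, muscle positions, visits and secondary outcomes as estimates with 95% confidence intervals and no significance claim.

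**In 2.11**, align the angle labels with the chosen measure, say which contrast and which sidedness the alpha of 0.05 refers to, and restate the power.

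**Cost.** The testing rule takes one paragraph and no patients. Under the fixed sequence the first contrast keeps its full 5%, but EGA vs CG cannot be claimed if EGB vs CG fails. Under the joint test, power for EGB vs CG falls from about 68–69% to about 56–63%, depending on where EGA lies. A Bonferroni split would cost more: about 60% power for two contrasts and 54% for three at 24 per arm (normal approximation). None of these restores 80%. A single two-sided contrast on the change score would need 31 per arm, or 35 with 10% loss (105 in all instead of 72). If the sample stays at 72, the lower power should be stated openly.

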## Discussion

3

Spasticity is the most prevalent motor disorder in cerebral palsy, and its management is intricate, posing a significant challenge for the rehabilitation team. While it may not be the primary factor hindering patient function, participation, or activity (5), it can play a crucial role in restricting their ability to move and perform daily life activities by interfering with limb function, leading to secondary pain from muscle spasms that may even disrupt sleep (6, 7). ESWT is a relatively new therapy in the field of neurology. In 2010, the first clinical trial applying focal shock waves for managing spasticity in patients with cerebral palsy was published (30). Over the recent years, it has established itself as an effective, non-invasive alternative with minimal side effects for spasticity management (11, 31, 32). Currently, there are limited published studies on ESWT for spasticity management in patients with cerebral palsy, and only 9 studies have investigated the effects of rESWT (16–24). The most studied muscle group has been the Triceps Surae, and there is significant disparity in the treatment doses applied in each study, especially regarding the number of sessions and the time interval between sessions. One of the most commonly used protocol is 3 sessions of rESWT with a one-week interval between each session (16, 21). Several features distinguish this study from previous ones. Despite the variability in dose administration, none of them have investigated the effect of rESWT by extending the time interval between sessions beyond 1 week to determine if therapeutic effects on spasticity can be prolonged by applying the same dose. Published studies have not followed up with patients beyond 12 weeks. In this study, we propose a follow-up of patients up to 24 weeks. Current literature indicates that a single session of shockwave therapy showed positive effects up to 4 weeks (17), and 3 sessions with a one-week interval between each session up to 12 weeks (16, 21, 22). Since our study hypothesis is that extending the interval between shockwaves sessions beyond 1 week may prolong the therapeutic benefit on spasticity, we deem it appropriate to extend the follow-up period to 24 weeks to observe potential differences between the study groups. In this study the physiological response of shock waves on the spastic muscle will be evaluated using MTS and pSWE, simultaneously, the functional response in overall mobility and gait of patients will be assessed using TUG and 10MWT. Furthermore, this is the first study to utilize GAS to define therapeutic goals that each patient wishes to achieve individually with rESWT application and analyze the success of therapy according to their specific improvement expectations for each set goal. If the study hypothesis is proven and an increased time interval between shock wave sessions extends therapeutic benefits on spasticity, it would be clinically significant, with the same treatment dose, patients could potentially benefit from shock wave effects for a longer duration. Additionally, this could provide patients and/or their caregivers with a broader range of scheduling options for treatment visits, for instance, it could improve accessibility for individuals who face geographical constraints or challenges in balancing work and family life. In such cases, the ability to attend treatment sessions every two or 4 weeks, instead of three consecutive weeks, could be more advantageous. The results of this study could have widespread implications for the cerebral palsy community, as they may be applicable to similar centers or institutions. Research on the effects of shock waves in reducing spasticity in patients with cerebral palsy opens up a promising avenue for future studies in this field.
